### **5.3. Criteria for subject discontinuation or completion**

If it is determined that continued observation of a subject is impossible due to the following reasons, that subject will be withdrawn from the study and the reason and date for this recorded. All necessary observations and tests will be performed at this time, and efficacy and safety evaluations performed.

- 1) Subject requests discontinuation or withdraws consent
- 2) A serious adverse event occurs which makes continuation problematic
- 3) Any event described in 6.3.3. occurs

- 4) Drug withdrawal lasts longer than 4 weeks
- 5) Any other reasons which lead the investigator/subinvestigator to consider continued participation problematic

Observation will also be discontinued for patients who discontinued taking study drugs.

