## **6.3 Handling of timepoints**

Results for blood pressure and degree of independence in activities of daily living (mRS) for timepoints between treatment allocation and 10 days after observation completion will be included in the analysis.

When summarizing the data for blood pressure and degree of independence in activities of daily living (mRS) according to observation timepoint, a range of dates is defined for use as each timepoint, regardless of the observation timepoint indicated in the case report form (Table 6-3). The observation start date is designated day 0, and the day before the observation start date is designated day -1. If multiple evaluation values are observed for a given timepoint, the value obtained closest to the specified date will be used. If the values are equally divergent from the specified date, the latest value will be used.

Table 6-3: Ranges of examination timepoints used in statistical analysis

| Timepoint                       | Specified
Day *1 | Range Used (day)                     |
|---------------------------------|--------------------------------|--------------------------------------|
| Day before
observation start | -1                             | *3 up to -1 *2 |
| 1 month                         | 30                             | 16 to 44 (± 2 weeks)                 |
| 3 months                        | 91                             | 63 to 119 (± 4 weeks)                |
| 6 months                        | 183                            | 127 to 239 (± 8 weeks)               |
| 12 months                       | 365                            | 309 to 421 (± 8 weeks)               |
| 18 months                       | 548                            | 492 to 604 (± 8 weeks)               |
| 24 months                       | 731                            | 675 to 787 (± 8 weeks)               |
| 30 months                       | 913                            | 857 to 969 (± 8 weeks)               |
| 36 months                       | 1,096                          | 1,040 to 1,152 (± 8 weeks)           |
| 42 months                       | 1,278                          | 1,222 to 1,334 (± 8 weeks)           |
| 48 months                       | 1,461                          | 1,405 to 1,517 (± 8 weeks)           |

\*1: Specified day calculated using 1 month =  $365.25/12 = 30.4375$

\*2: Including 0 if preliminary examination performed

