## 6.4 Handling of missing data

Missing data will not be imputed.

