## 7. DISPOSITION OF PATIENTS

The follow data summaries will be prepared for all subjects allocated to a treatment (ITT).

For the subjects for whom observations are discontinued or completed, the numbers of subjects observed for 1 year and 2 years and frequency distributions of the reasons for discontinuation/completion will be determined for each treatment group.

Discontinuation of observations: When the following criteria for discontinuation/completion are met and observations are discontinued.

Discontinuation/completion criteria

- 1) The subject requests that their study participation be discontinued or withdraws their consent

- 2) A serious adverse events occurs, making continued study participation difficult
- 3) An evaluated event occurs
- 4) The study drug is continuously withdrawn for more than 4 weeks
- 5) The investigator/subinvestigator otherwise determines that the subject's continued study participation would be difficult

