## 10.7 Other safety endpoints

### Degree of independence in activities of daily living (mRS)

Evaluate as one of following 7 levels according to Japanese Modified Rankin Scale (Japanese Guidelines for Management of Stroke 2009). A frequency distribution will be determined for each treatment group and timepoint, and a shift table will be prepared for the values at each timepoint before and after the start of the observation for each treatment group.

0. No symptoms at all
1. No significant disability despite symptoms: able to carry out all usual duties and activities
2. Slight disability: unable to carry out all previous activities, but able to look after own affairs without assistance
3. Moderate disability: requiring some help, but able to walk without assistance
4. Moderate to severe disability: unable to walk without assistance and unable to attend to own bodily needs without assistance
5. Severe disability: bedridden, incontinent and requiring constant nursing care and attention
6. Dead

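### The follow-up mRS tables include a grade for death, but a known death can appear in at most one row and is missing from every later row

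*Supplement*

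**What the plan says.** SAP 10.7 lists mRS under other safety endpoints, on the seven-level scale whose last grade is death. "A frequency distribution will be determined for each treatment group and timepoint", and a shift table is added. No test is planned.

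SAP 6.3 and Table 6-3 set a specified day and a window for each row. Readings "between treatment allocation and 10 days after observation completion will be included in the analysis". Within a window, "If multiple evaluation values are observed for a given timepoint, the value obtained closest to the specified date will be used", and "If the values are equally divergent from the specified date, the latest value will be used". SAP 6.4 adds: "Missing data will not be imputed".

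SAP 7 lists among the reasons for ending observation: "An evaluated event occurs". SAP 6.2.5 counts death, ischemic stroke, intracerebral hemorrhage, subarachnoid hemorrhage, TIA, myocardial infarction and other vascular events as evaluated events. Protocol 5.3 goes further: "Observation will also be discontinued for patients who discontinued taking study drugs".

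No section says whether or on what date a grade 6 is entered for a death, or that it is carried to later timepoints. The date of death is collected (Protocol 6.3.3), and death from any cause is a secondary endpoint with its own time-to-event analysis (SAP 9.2.4).

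**The concern.** Death is an absorbing state. Once its date is known, the mRS grade at every later specified day is known to be 6, so entering it is not imputation of an unknown value. The plan handles it as a single reading that falls into one window and is then lost. The table therefore has a column for death that omits most deaths to date.

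A reader would naturally take the month-24 or month-36 row as the functional state of the arm at that time. If mortality differed between arms, the arm with more deaths would look too good in these rows, and the shift table would miss most moves to grade 6.

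**Working it through.** **1. Windows.** Specified day = months × 30.4375, rounded; half-width 14, 28, then 56 days. This reproduces all ten rows of Table 6-3 (month 6: day 183, 127 to 239; month 12: day 365, 309 to 421; month 24: day 731, 675 to 787). The windows do not overlap. They leave out days 1-15, 45-62, 120-126, 240-308, 422-491, and then 69 or 70 days in each half-year.

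**2. One row at most.** Assume a 6 is entered and dated on the day of death.
- Death on day 160 with no closer reading: shown at month 6, absent from month 12 on.
- Death on day 270: in the 240-308 gap, shown nowhere.
- Visit on day 185 with mRS 1, death on day 200: the distances from day 183 are 2 and 17, so month 6 shows mRS 1. The subject was alive on day 183, so that value is right. The loss begins at month 12.

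**3. Is the closest-day rule the cause?** Let s be the specified day, d the day of death and v an earlier living reading. If d ≤ s, then v < d ≤ s, so s − v > s − d and the death is chosen. A living reading can win only when d > s, that is, when the subject was alive on the specified day. Simulation gave no displacement of a death dated on or before s.

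**4. Ceiling per row.** With deaths spread evenly over time and every in-window death displayed, the share of deaths up to the close of the window that the row can show is window length / last day of window:
- month 3: 57/119 = 48%
- month 12: 113/421 = 27%
- month 24: 113/787 = 14%

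With living visits exactly on the specified day, month 12 falls to 57/421 = 14% and month 24 to 57/787 = 7%.

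**5. Size under assumed rates.** The documents give no mortality rate. Assume death λ = 1% per year (range 0.5% to 2%) and other exits μ = 10% per year. The second is in keeping with the plan's own 4% or 2.8% recurrence plus 5% dropout (9.0% or 7.8%), before other evaluated events and stopping of study drug.
- True share dead = 1 − exp(−λt).
- Shown in the row: between λ × 57/365.25 = 0.16% (visits exactly on the day) and λ × 113/365.25 = 0.31% (every in-window death shown). Simulation gives about 0.2% in each row.
- Carried forward = D/(D + S), with S = exp(−(λ+μ)t) and D = [λ/(λ+μ)] × (1 − S).

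| Month | True | Shown under the plan | D | S | Carried forward |
|---|---|---|---|---|---|
| 12 | 1.0% | about 0.2% | 0.0095 | 0.896 | 1.05% |
| 24 | 2.0% | about 0.2% | 0.0180 | 0.803 | 2.19% |
| 36 | 3.0% | about 0.2% | 0.0256 | 0.719 | 3.43% |

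Simulation with visits spread inside the windows puts the last column at 1.1%, 2.2% and 3.5%. At month 36, λ = 0.5% gives 1.5% true, 0.08% to 0.15% shown and 1.7% carried forward. λ = 2% gives 5.8% true, 0.3% to 0.6% shown and 6.7% carried forward.

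**6. Deaths in no row.** With deaths spread evenly over 48 months (1,461 days), the windows cover 29 + 57 + 7 × 113 + 57 = 934 days, or 64%; the other 36% of deaths fall outside every window. A closer living reading takes the row from a further 15% to 30%, depending on visit timing, always after that row's specified day. So 51% to 66% are shown nowhere over 48 months, and 44% to 70% across follow-up horizons of 421 to 1,643 days. At the rates in step 5, with visits within half of the allowed window, the share is about 55% to 60%.

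**The case against.** The best case for leaving the plan alone has four parts.

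- **The table is as-observed by choice.** mRS during follow-up is an untested descriptive item, and death is compared by log-rank test, Kaplan-Meier curves and hazard ratio. A mortality imbalance would be seen there. This stands and limits the weight of the point.
- **Grade 6 may be scale boilerplate.** The same 0-to-6 list appears for baseline characteristics (SAP Table 8.1) and subgroups (SAP Table 6.8), where nobody can be dead. This is a fair reading of those tables. SAP 10.7, however, applies the scale after the start of observation, when deaths do occur, and nothing tells the reader to ignore the last column.
- **Living subjects leave too.** Evaluated events and stopping of study drug remove far more subjects than death does at the assumed rates. Carrying deaths forward while these subjects leave overstates the share dead, by about half a percentage point at month 36 (3.4% to 3.5% against 3.0%). This stands and calls for a labelled denominator. The error is still much smaller than showing 0.2%.
- **The magnitude rests on assumptions.** The mortality, exit rate and visit timing are not in the documents. The limit of one row per death does not depend on them.

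A reader might also infer that the closest-day rule favours living readings and so erases deaths. It does not: step 3 shows that it never displaces a death dated on or before the specified day, and ties go to the later value. If anything, a death just after the specified day can be shown as 6 one row early.

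**Conclusion.** The point holds as a minor one. Under the written rules a death during observation appears in at most one mRS row and in no later row. From month 3 on, with deaths evenly spread, each row shows under half of the deaths to date; at month 24 it shows 14% at most. At 1% per year mortality and 10% per year other exits, about 0.2% are shown dead where the truth is 1.0%, 2.0% and 3.0% at months 12, 24 and 36. All of this assumes that a 6 is entered on the date of death. If it is not, the column is emptier still.

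Two stronger readings are tempting. One is that the rows describe survivors only; they describe subjects under observation with a reading in the window, they can contain some 6s, and they also exclude living subjects whose observation has ended. The other is that the shift table cannot show a move to death; it can show some, but would miss most. Neither the primary analysis nor the analysis of all-cause death is affected.

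**What to change.** Add to SAP 6.3 and 6.4: for mRS, a subject who died during observation is assigned grade 6 at every specified day on or after the date of death, up to that subject's administrative end of follow-up. State that the 6 is dated on the day of death. No priority clause over the closest-day rule is needed.

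In the SAP 10.7 tables, show per arm and row the number under observation with a reading and the number dead. Label the denominator, because living subjects whose observation ended early are not in it and the share dead is therefore slightly overstated.

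If the rows are meant to be purely as-observed, the smaller change is to drop grade 6 from the follow-up tables, label the rows as subjects under observation, and print cumulative deaths beside them.

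Either costs a sentence or two and a few lines of programming. The death date is already collected, so no new data are needed.

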## 6.4 Handling of missing data

Missing data will not be imputed.

## 6.5 Significance level and confidence coefficient

Because the evaluation of superiority with respect to the primary endpoint will be based on repeated tests, including the interim analysis, an increase in type I errors resulting from multiplicity will occur. Therefore, significance levels (two sided) will be selected using the Haybittle-Peto ad-hoc method.

Interim analysis significance level: 0.0027 (corresponds to  $z = 3$ )

Significance level for final analysis: 0.05

The significance level of the tests used in the other efficacy and safety evaluations will be a two-sided level of 5%. A two-sided significance level of roughly 5% will also be used for other evaluations, although an explicit significance level will not be established.

The confidence coefficient used for the estimates will be 95% (two sided).

## 6.6 Multiple comparisons/multiplicity

A significance level (two sided) determined using the Haybittle-Peto ad-hoc method will be used to examine superiority with respect to the primary endpoint.

No multiplicity adjustment will be performed for the efficacy endpoints other than the primary endpoint or for tests and estimates of the safety endpoints.

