### 11.3. Analysis items and methods

Demographic characteristics of patient backgrounds will be calculated for each group in the ITT analysis population. Continuous variables are shown as mean (standard deviation) or median (quartile ranges), while category variables are shown as number of subjects (percentage) per category. Mean and median values will also be calculated for length of subject observation periods. Intergroup bias will also be studied with appropriate tests based on variable characteristics.

Kaplan-Meier plots will be drawn by group for the primary endpoint of ischemic stroke recurrence, while groups will be compared with the log-rank test. Also, the Cox proportional hazards model will be used to calculate hazard ratios and 95% CIs for DAPT groups versus SAPT groups. Unadjusted hazard ratios and adjusted hazard ratios [adjusted according to age, sex, clinical type of cerebral infarction (atheroma or lacunar), and mRS] will be calculated at this time.

Annual recurrence rates will be calculated with both person-year and Kaplan-Meier methods, 95% CIs for which will be calculated with the approximate Poisson and Greenwood methods.

Subgroup analysis will include the following factors: age, sex, antiplatelet therapy (aspirin or clopidogrel), clinical subtype of ischemic stroke (atheroma or lacunar), presence or absence of 50% or greater stenosis of

extracranial arteries, mRS, medical history and complications (hypertension, diabetes mellitus, dyslipidemia, coronary heart disease, peripheral artery disease, chronic kidney disease, and ischemic stroke), smoking status, and BMI. Continuous variables will be divided at the median, at which point a Cox proportional hazards model including a comparison group, predictive factors, and interactions will be studied. Stratified hazard ratios of the combination group compared to the SAPT group will be calculated according to predictive factors. Uniformity of interactions will also be studied. Significance level for all statistical tests is bilateral 5%.

Details of statistical analysis are described in the statistical analysis protocol authored by the Statistical Analysis Committee and the analysis officers in charge of the final analysis in the data center.

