### **9.2.1 Stroke (ischemic stroke, intracerebral hemorrhage, subarachnoid hemorrhage)**

The first event involving ischemic stroke, intracerebral hemorrhage, or subarachnoid hemorrhage will be included in the analysis.

Subjects discontinued for reasons other than occurrence of an event included in the analysis and subjects who continue to study completion will be considered censored subjects. The censor date will be considered the observation completion date.

- 1) A between-groups comparison for the period from the observation start date to the date of ischemic stroke onset will be performed using the log-rank test, and the superiority of the combination therapy group versus the monotherapy group will be examined.
- 2) Survival coefficients for the period from the observation start date to the date of the event will be estimated for each treatment group using the Kaplan-Meier method and plotted.
- 3) The hazard ratio for the occurrence of an event in either of the 2 groups and its 95% confidence interval will be determined using the Cox proportional hazard model.

The same analysis described in section 9.2.1 will be performed for the events indicated in sections 9.2.2 to 9.2.6.

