### **9.2.3 Ischemic cerebrovascular disorder (ischemic stroke, TIA)**

The first event involving ischemic stroke or TIA will be included in the analysis.

Subjects discontinued for reasons other than occurrence of an event included in the analysis and subjects who continue to study completion will be considered censored subjects. The censor date will be considered the observation completion date.

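### All six secondary endpoints are tested for superiority of DAPT at two-sided 5% with no gate on the primary result and no exploratory label, so a false secondary superiority result has roughly a 9 to 11% chance

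*Supplement*

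**What the plan says.** The primary test is clearly set out. SAP 9.1 compares time to recurrent ischemic stroke by log-rank test, and SAP 6.5 and 6.6 control that one decision by the Haybittle-Peto method ("Interim analysis significance level: 0.0027", and 0.05 at the final analysis).

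For the secondary endpoints, four statements work together:

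- SAP 9.2.1, item 1, describes a log-rank comparison in which "the superiority of the combination therapy group versus the monotherapy group will be examined". SAP 9.1 states the aim of the primary test in the same terms.
- SAP 9.2.1 closes with "The same analysis described in section 9.2.1 will be performed for the events indicated in sections 9.2.2 to 9.2.6". That makes six such tests: any stroke; ICH or SAH; ischemic stroke or TIA; death from any cause; stroke, MI or vascular death; and all vascular events.
- SAP 6.5: "The significance level of the tests used in the other efficacy and safety evaluations will be a two-sided level of 5" per cent. Protocol v1.3, section 11.3, agrees: "Significance level for all statistical tests is bilateral 5" per cent.
- SAP 6.6: "No multiplicity adjustment will be performed for the efficacy endpoints other than the primary endpoint". The same sentence extends this to the safety endpoints.

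The list in SAP 9.2 is numbered, but nothing makes the numbering a testing order. Neither document makes a secondary test conditional on the primary result or calls these analyses exploratory, supportive or descriptive. Protocol 11.3 describes the between-group efficacy comparison only for the primary endpoint, so it does not fill the gap.

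**The concern.** Leaving secondary endpoints unadjusted is unobjectionable when the plan also says that their results are descriptive. This plan omits that statement and names superiority as the aim of each test. SAP 6.5 recognises that repeated testing inflates type I error and deals with it for the primary endpoint. SAP 6.6 then leaves six further tests with the same stated aim uncontrolled.

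What is at stake is interpretation. If the reduction in ischemic stroke is not significant, nothing in the plan prevents a p<0.05 on, say, death or all vascular events from being reported as a prespecified superiority finding. Its error rate would then be higher than the nominal level suggests.

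**Working it through.** **The plan's own figure.** The documents give no family-wise error rate for the secondary endpoints. The one error figure that can be checked is the interim level: 2 × (1 − Φ(3)) = 0.0027, as stated in SAP 6.5.

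**Inputs from the documents.** Six tests (SAP 9.2.1 to 9.2.6), each at two-sided 5%, which is 2.5% in the direction favouring DAPT. Ischemic stroke is a component of four of the six (9.2.1, 9.2.3, 9.2.5, 9.2.6); for instance 9.2.3 says "The first event involving ischemic stroke or TIA will be included in the analysis". The assumed ischemic stroke rates are 4% and 2.8% per year (SAP 4), with mean (4 + 2.8)/2 = 3.4%. The calculation takes each endpoint's own event as the outcome, although item 1 of 9.2.1 speaks of ischemic stroke onset where items 2 and 3 speak of the event.

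**Step 1: independent tests, as an upper reference.**
- Either direction: 1 − 0.95^6 = 0.265.
- Favouring DAPT: 1 − 0.975^6 = 0.141.

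**Step 2: allowing for shared events.** The composites overlap, so the test statistics are correlated. Under the global null, the correlation of two log-rank statistics was taken as (shared events)/√(d_i × d_j), where d_i and d_j are the event totals of the two endpoints. The documents give no rates for the other components. The assumed base case, in % per year, is: ischemic stroke 3.4, ICH/SAH 0.5, TIA 0.4, MI 0.3, vascular death 0.3, non-vascular death 0.6, other vascular events 0.8. Two examples:
- Any stroke (3.4 + 0.5 = 3.9) with ischemic stroke or TIA (3.4 + 0.4 = 3.8): 3.4/√(3.9 × 3.8) = 0.88.
- Any stroke (3.9) with ICH/SAH (0.5): 0.5/√(3.9 × 0.5) = 0.36.

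Four other mixes were run. Across all five, the rates covered ischemic stroke 2 to 3.4, ICH/SAH 0.2 to 1.5, TIA 0.1 to 2, MI 0.1 to 1.5, vascular death 0.1 to 1, non-vascular death 0.3 to 1.5 and other vascular events 0.3 to 4. Each mix used 1,000,000 draws from the multivariate normal distribution.

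| Event under the global null | Base case | Range over five mixes | If independent |
|---|---|---|---|
| At least one secondary significant in favour of DAPT | 9.4% | 8.6 to 10.7% | 14.1% |
| At least one secondary significant, either direction | 18.3% | 16.8 to 20.9% | 26.5% |
| At least one secondary significant, either direction, and primary not significant | 13.8% | 12.0 to 17.1% | – |
| Secondary and primary both significant in favour of DAPT | 2.2% | 1.9 to 2.4% | – |

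**Step 3: what a gate removes.** In the base case, false DAPT-favouring secondary results without a primary result favouring DAPT occur with probability 9.4% − 2.2% = 7.2%. At the extremes the figures are 8.6% − 2.4% = 6.2% and 10.7% − 1.9% = 8.8%. A gate on the primary result blocks all of these and leaves about 2%. A gate alone does not protect the secondary endpoints when the primary effect is real, so a fixed sequence or Holm step is still needed behind it. Holm over six tests starts at 0.05/6 = 0.0083. With gate and procedure together, the family-wise error over primary and secondary endpoints is at most 5% at the final analysis.

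**The case against.** The strongest reply is that this is a disclosed choice. There is one primary endpoint, the six others are called secondary throughout, and SAP 6.6 says openly that they are not adjusted. That is common practice, and it breaks no statement elsewhere in the plan. SAP 9.2.1 says superiority will be examined, not concluded, and item 3 already requires a hazard ratio with 95% CI for each endpoint. All of this stands. It makes the point a cheap improvement rather than an error, but it does not supply the missing rule for a secondary p<0.05 after a failed primary.

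Three stronger readings are tempting, and the documents do not support them:

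- **A false superiority risk of about 20%.** That figure counts significance in either direction. About half of those results would favour SAPT and could not be claimed as superiority of DAPT.
- **Inflation of the primary error rate.** The secondary tests play no part in the primary decision, which SAP 6.5 and 6.6 handle separately.
- **ICH/SAH has no place in a superiority test because the background argues only that bleeding does not increase.** Protocol 2.2 also reports that cilostazol alone halved serious bleeding against aspirin. The ICH/SAH test is two-sided, so it can show harm as well as benefit. Severe or life-threatening hemorrhage, which includes intracranial bleeding, is separately compared as a safety endpoint in SAP 10.5.

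**Conclusion.** The point holds as a gap in the rules for interpreting the secondary endpoints. Under the global null, the chance of at least one false DAPT-superiority result is about 9 to 11%, roughly four times the 2.5% of a single test (9.4/2.5 = 3.8), and 14.1% if the tests were independent. In either direction it is about 17 to 21%, or 26.5% if independent. Only the independent-test figures follow from the documents alone; the others depend on the assumed event mix.

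A reader might infer that the sponsor intends to claim a secondary benefit in place of a failed primary. No passage says so; the plan merely does not rule it out.

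**What to change.** Amend SAP 6.6 and 9.2 before results by group are known, in one of two ways:

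1. **Gate and procedure.** State that superiority on a secondary endpoint may be claimed only if the primary log-rank test is significant, and then only through a prespecified fixed sequence or Holm procedure. The choice of procedure and the order belong to the sponsor.
2. **Exploratory label.** State that the secondary analyses are exploratory and reported as hazard ratios with 95% CIs, and delete the superiority wording from 9.2.1.

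ICH/SAH may stay a secondary endpoint with its hazard ratio and CI under either option.

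The cost is a few sentences. Sample size, data collection and the primary analysis do not change. The small downside is that an isolated secondary p<0.05 can no longer be called superiority. Under a fixed sequence, an endpoint placed late may also go formally untested after an earlier non-significant result.
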